#### Farmer Task

While in the MRI environment, participants completed the farmer task [80]. In this gamified task, the participant is asked to take on the role of a farmer whose task is to travel between a shed and garden to harvest crops. Two different roads connect the shed to the garden: (1) a short road and (2) a long road. Traveling the short road is perilous (contingently associated with an electric shock; 3-5 mA for 100 ms) but allows the farmer quick travel from shed to garden, thereby assuring a successful harvest. Conversely, traveling the long road is always safe (never associated with shock) but often prevents the farmer from arriving at the garden before “wild birds” eat the crop.

Before each trial, a stimulus is presented to the participant that they learn can indicate whether the short road will deliver the electric shock. Specifically, participants learn, through fear conditioning, that shock is predicted by a visual ring of extreme size (conditioned danger cue: CS+) but not by rings of the smallest size (conditioned safety cue: CS–) displayed on the screen. During the game, rings of intermediary sizes, presented in the absence of a shock, serve as generalization stimuli. The task captures fear generalization and subsequent instrumental avoidance by assessing task-based behaviors in response to generalization stimuli that are similar (but not identical) to CS+. Decisions to “unnecessarily” avoid during safe cues is considered *maladaptive* because danger (threat of shock) is not a realistic possibility, and avoiding unnecessarily compromises performance on the task. Adaptive responding is operationalized by higher rates of decisions to push through (ie, low levels of avoidance) when encountering safe yet danger-resembling cues.

### DNA Samples

All participants enrolled in the longitudinal study were asked to provide a DNA saliva sample at baseline, which is stored for future analysis. Participants in the laboratory substudy are also asked to provide a blood sample to be stored for future research.

### Administrative Data

The study team will work with the local National Guard to extract administrative data capturing sociodemographic and service-related variables (ie, Armed Forces Qualification Test score, training dates, and military discharge). Administrative data from military records will be deidentified and matched by participant ID.

### Sample Size and Power Analysis

Sample size was calculated based on the primary objective of the study (aims 1 and 2) using structural equation models of various hypothesized structures (nested and longitudinal). This demand resulted in a sample size that could provide sufficient power to test such hypotheses across varying df. Control of root mean square error of approximation (RMSEA) was the criteria used for our sample size and power calculations. According to MacCallum and colleagues [81], RMSEAs of 0.01, 0.05, and 0.08 indicate excellent, good, and mediocre fit, respectively. Table 4 presents the required sample sizes and the corresponding powers for df=2 and df≥5, assuming a null RMSEA of 0.05 and an α of .05. Assuming a retention rate of 65% to reach an effective sample size of 780, we needed to recruit 1200 participants. Note that for n=780, structural equation models with df≥5 would have an expected power of at least 0.909. The column for df=2 demonstrates that for df smaller than 5, the power for our feasible sample size drops below conventional 0.80.

**Table 4 table4:** Power estimates (chi-squared test for root mean square error of approximation=0.05).

Sample size	Estimate (*df*)	Estimate (*df*)
700	0.567 (2)	0.878 (5)
800	0.619 (2)	0.916 (5)
1000	0.707 (2)	0.961 (5)
1200	0.776 (2)	0.982 (5)

### Data Management

Data collected via the web-based survey platform (Qualtrics) administered at the UMN will be downloaded securely into the study databases stored on a shared server at the MVAHCS, with access limited to authorized study personnel. Qualtrics includes a complete suite of features to support Health Insurance Portability and Accountability Act compliance, including a full audit trial, user-based privileges, and integration with the institutional Lightweight Directory Access Protocol (LDAP) server. Hard copy surveys will be double entered and checked for consistency. Laboratory substudy data (ie, neuroimaging and EEG data) will be stored in secure databases held on servers at the UMN and will be available only to lead investigators of each substudy component and the principal investigator. Administrative data will be transferred directly from the Minnesota Army National Guard to a secure server at the MVAHCS via secure data transfer. At the MVAHCS, the data will be accessible by a named Center for Care Delivery and Outcomes Research (CCDOR) Data and Statistics Team member. This individual will deidentify the personal information, match records with the study ID number, and transfer them to a shared server for the study. The study ID numbers will be used for data transfer, communication, and analysis purposes to protect confidentiality. Participant contact information linked with the study ID number will be stored in an SQL server database that will be created on internal Department of Veteran Affairs (VA) web servers. Only individuals with a need to access the data, as vetted by the principal investigator, will be granted access. Access to contact information will be obtained through Windows authentication (ie, personal identity verification card and password for the network).

### Statistical Methods

Aim 1 will characterize adaptation among young military recruits over the first 2 years of service. Consistent with a hierarchical concept of the structure of resilience, we will use latent growth mixture modeling to identify the latent trajectories of adaptation and its indicators. We will apply latent growth mixture modeling at the level of internalizing symptoms, externalizing problems, and social-occupational functioning as well as an overall model that simultaneously embeds all 3 domains into a model of adaptive functioning. We hypothesize that at least three trajectories (one showing resilient adaptive functioning or low pathology and the other two showing new-onset and chronic distress) will emerge for each domain assessed (internalizing symptoms, externalizing problems, social-occupational functioning, and global adaptive functioning).

Note that all remaining analyses for aims 2 and 3 will be conducted on the trajectory class membership data for each of these 4 domain outcomes to test for the specificity of resilience mechanisms***.***

Aim 2 will identify the promotive factors and protective processes contributing to individual variations in adaptation. We will apply structural equation modeling and Bayesian network analysis to detect and identify the latent constructs and the dependency structure between different domains. We will also examine the effects of protective and vulnerability factors on membership in different trajectory classes. We propose to investigate this in 2 complementary ways. First, in our structural equation modeling, we will augment the measurement submodels of the most parsimonious latent growth structural mixture models accepted in aim 1 with the indicators of protective and vulnerability measurements (Tables 1 and 2) and evaluate the change in the relationships (coefficients) that indicators have with the latent trajectories. We will treat potential predictors as moderators or mediators, depending on their hypothesized role in the model, and we will test their contribution to the model by change in model fit indices using the Akaike information criteria (AIC), the Bayesian information criteria (BIC), root mean squared error (RMSE), and goodness-of-fit (G^2^) also known as the likelihood ratio test. Second, the trajectory class membership assignment in aim 1 will be used as dependent variables (resilient vs nonresilient or distressed trajectories), and protective and vulnerability factors will be used as predictors in random intercept multinomial logistic mixed models that will provide a quantitative picture of the unique contribution of these measures. We hypothesize that the risk factors listed in Tables 1 and 2 will predict membership in nonresilient or distressed trajectory classes, whereas protective or promotive factors will predict membership in the resilient or nondistressed trajectory classes. All analyses will be estimated within the propensity classes that adjust for any possible lack of imbalance and will be performed on both complete cases and 5 imputed data sets.

Aim 3 will investigate whether neurobehavioral markers of self-regulation assessed using a series of performance-based tasks involving EEG and fMRI assessments are predictive of resilient and nonresilient trajectories. EEG recordings will be put through an independent component analysis–based processing pipeline to isolate and remove noisy time segments, signal artifacts (eg, eye movements), and bad electrodes. Recording epochs centered around the onset of task stimuli will be extracted for the analysis of event-related potentials and time-frequency energy. Given that this study focuses on conflict monitoring and bottom-up covert attention, we plan to examine brain responses at midline frontal (eg, FCz) and lateralized posterior electrodes (eg, PO7 and PO8), respectively. We will quantify brain response metrics such as feedback-related negativity and θ-band (4-8 Hz) oscillations, which we predict will be associated with trajectory class membership. fMRI data collected during the farmer task will be analyzed using an event-related design to model blood oxygenation level dependent (BOLD) fluctuations due to stimuli onsets using Analysis of Functional Neural Images software [82]. Functional activation maps will be computed by regressing each voxel’s fMRI response time course onto an ideal response function for 5 stimulus types: the danger cue, 3 classes of safety cues with parametrically varying levels of perceptual similarity to the danger cue, and a control condition including a safety cue with no perceptual similarity to the danger cue [83]. We will focus particularly on fMRI responses to these stimuli in brain areas associated with fear reactivity (anterior insula and dorsomedial prefrontal cortex) and fear inhibition (ventromedial prefrontal cortex and anterior hippocampus). Fear-related brain activations to safety cues resembling danger cues (relative to safety cues without danger-cue resemblance) will be used as predictors of maladaptive avoidance (costly or unnecessary avoidance of safe cues perceptually resembling danger cues). Finally, these brain and behavioral responses, as well as their moderation by protective (eg, social support, military cohesion, and self-regulation) and vulnerability factors (eg, BCT stressors and anxiety traits), will be used as predictors of trajectory class membership.

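### The plan says it will test specificity of mechanisms by repeating analyses over four outcomes, but names no comparison of a predictor's effect between domains

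*Protocol article*

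**What the plan says.** All references are to the protocol article.

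- **Statistical Methods, aim 1.** Growth mixture models are fitted to each of three domains, and there is also "an overall model that simultaneously embeds all 3 domains into a model of adaptive functioning". This gives four outcomes: "internalizing symptoms, externalizing problems, social-occupational functioning, and global adaptive functioning".
- **Statistical Methods, note after aim 1.** All aim 2 and aim 3 analyses use class membership "for each of these 4 domain outcomes to test for the specificity of resilience mechanisms". One sentence gives both the goal (a test of specificity) and the means (running the analyses for each outcome).
- **Statistical Methods, aim 2.** Of the measures thought to protect or to add risk, the text says that they "will be used as predictors in random intercept multinomial logistic mixed models that will provide a quantitative picture of the unique contribution". The dependent variable is resilient versus nonresilient or distressed class. Predictors added to the structural equation models are judged by change in fit (AIC, BIC, RMSE, likelihood ratio). The only explicitly cross-domain step is structural equation modelling and "Bayesian network analysis to detect and identify the latent constructs and the dependency structure between different domains".
- **Statistical Methods, aim 3.** Brain and behavioral responses, and their moderation by other factors, predict class membership. No between-domain contrast is named.
- **Sample Size and Power Analysis.** Power is given for model fit only: "for n=780, structural equation models with df≥5 would have an expected power of at least 0.909".

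**The concern.** A mechanism is specific to a domain if its effect there differs from its effect elsewhere. That is a statement about a difference between coefficients. Running the same predictor model for each outcome gives an estimate and a test against zero for each, which is a different question. One domain can reach significance and another fall short when both effects are the same size. Conversely, two domains can both be significant while their effects differ.

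The four outcomes are also not on the same level. The global outcome is built from the other three, so its agreement with any one of them is partly a matter of construction.

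At stake is which factors get reported as acting on internalizing, externalizing or social-occupational adaptation. The Conclusions say the findings should inform prevention and intervention strategies.

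**Working it through.** **1. The plan's own power figure, and what it covers.** Recruitment: 780 / 0.65 = 1200, as stated ("Assuming a retention rate of 65% to reach an effective sample size of 780, we needed to recruit 1200 participants"). The RMSEA power comes from the noncentral chi-square with noncentrality (n − 1) × df × RMSEA², "assuming a null RMSEA of 0.05 and an α of .05". At n=780 and df=5 this gives 0.909, and it matches all eight entries of Table 4 to within 0.001, if the alternative RMSEA is taken as 0.10 (the text does not state the alternative). The figure is thus reproduced, but it describes model fit. It says nothing about power for one predictor or for a between-domain difference, so those have to be assumed.

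**2. Equal true effects, independent estimates.** Let p be the power in each of the three component domains. The chance that at least one but not all three are significant is 1 − p³ − (1 − p)³.

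- p = 0.50: 1 − 0.125 − 0.125 = 0.75
- p = 0.80: 1 − 0.512 − 0.008 = 0.48
- p = 0.90: 1 − 0.729 − 0.001 = 0.27

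**3. Equal true effects, correlated estimates.** All domains are measured in the same people, so correlation is expected. Simulation of three z-statistics with equal means (400,000 draws, two-sided 0.05) gives these chances of a mixed pattern:

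| Power per domain | correlation 0 | 0.3 | 0.5 | 0.7 |
|---|---|---|---|---|
| 50% | 75% | 61% | 50% | 38% |
| 80% | 48% | 40% | 34% | 26% |
| 90% | 27% | 24% | 20% | 16% |
| 95% | 14% | 13% | 11% | 9% |

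**4. Translation to the study's sample sizes.** Logistic simulation of class membership, with an assumed 20% nonresilient share, the same odds ratio (OR) per SD in all three domains, and latent correlation 0.3 or 0.6. There were 600 runs per setting, so the Monte Carlo standard error is at most √(0.25/600) = 0.02.

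| N | OR per SD | power per domain | mixed pattern (0.3 / 0.6) |
|---|---|---|---|
| 780 | 1.2 | 50% to 54% | 63% / 59% |
| 780 | 1.3 | 81% to 85% | 39% / 33% |
| 780 | 1.5 | over 99% | 1.5% / 1.2% |
| 123 | 1.5 | 37% to 41% | 62% / 52% |
| 123 | 1.8 | 69% to 73% | 57% / 50% |

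The Strengths and Limitations section speaks of power for small effects but gives no number, so the odds ratios are assumptions. The laboratory substudy was enriched for high risk, so its nonresilient share may exceed 20%.

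**5. The global outcome.** If a factor acts on one domain only, with 80% to 99% power there, an equal-weight composite of the three is also significant in 21% to 70% of simulated studies (correlation 0.5 down to 0). The global result is therefore not separate evidence. Nor is it what drives the mixed pattern: adding it as a fourth outcome under equal effects at 80% power moves the chance only from 47.9% to 48.6% (correlation 0) or from 26.3% to 26.6% (correlation 0.7). The largest change seen is at 50% power and correlation 0, from 75.1% to 82.2%.

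**6. A direct test.** A 2-df Wald test that the three effects are equal, on the same kind of z-statistics, rejects in 4.9% to 5.0% of draws when they are equal. This calculation does not include error in class assignment.

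**The case against.** **No decision rule is written.** A reader might infer that the plan will declare mechanisms domain-specific whenever verdicts differ. The text does not support that: it never says how results from the four outcomes will be compared, and an article may leave such detail to a fuller plan. This part of the objection stands. The concern is limited to the fact that the article does name a means for its specificity test, and that means contains no comparison.

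**Joint estimation is not excluded.** The overall model holds all three domains, and the fit comparisons could carry equality constraints. The random intercept could mean domains stacked within person, since each person has one class per domain. But the unit of the random intercept is not stated and could be the recruitment unit. The fit indices are described as judging a predictor's contribution, and the network step concerns dependence between domains. Even a stacked model would need a predictor-by-domain term, and none is named.

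**The overlap is intended.** The section adopts a hierarchical concept with a global level above its domains. A reader might infer that containing the other three outcomes makes equal effects look specific. That does not follow: when a factor acts on one domain, the overlap pushes the global result towards agreement with it. The overlap is a second, separate point.

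**Joint modelling is harder than it sounds.** Each domain may have its own number and meaning of classes, and unequal classification error can attenuate coefficients unequally, so a naive equality test can reject when effects are equal. This stands and shapes the fix.

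**Specificity is a side aim.** It appears in neither the Objectives nor the aim 2 hypothesis. That limits the reach of the point to specificity claims; the per-domain analyses themselves are unaffected.

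**Conclusion.** The concern holds in limited form. The Statistical Methods section states a goal of testing specificity and a means that tests each effect against zero, and nothing in aims 2 and 3 compares a predictor's effect between domains. This invites, but does not prescribe, reading differing significance as specificity.

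With equal true effects in the three component domains, differing significance would arise in about 26% to 48% of studies at 80% power per domain and 38% to 75% at 50% power. The upper ends assume independent estimates, which is unlikely within the same people. The size depends on assumed power, correlation, effect size and class share, none of which the document gives. It nearly vanishes for large effects at N=780 (1% to 2% at an odds ratio of 1.5). It is roughly one in three to two in three for smaller effects at N=780 (odds ratio 1.2 to 1.3), and about one half or more in the 123-person substudy under the settings tried.

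The global outcome is not an independent comparator, but it is not the cause of the mixed patterns.

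**What to change.** For specificity claims only:

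1. Code each of the three component domains on the resilient versus nonresilient contrast that aim 2 already uses, so that coefficients are comparable even if the class solutions differ.
2. Fit one joint model of the three domains with person-level clustering, and test equality of each predictor's effect across domains (predictor by domain).
3. Allow for class-assignment error, for example by posterior-probability weighting or a bias-adjusted three-step approach.
4. Base specificity claims on the estimated between-domain difference and its interval, not on one domain being significant and another not.
5. Report the global outcome as a summary, outside that comparison.

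If the random intercept was meant to stack domains within person, saying so and adding the predictor-by-domain term would cover step 2.

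Cost: wording in the analysis plan and some extra modelling, with no new data. Tests of differences have less power than tests against zero, so fewer specificity claims will be possible, above all in the laboratory substudy.

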Drawing on the aforementioned literature, the Advancing Research on Mechanisms of Resilience (ARMOR) study was established at the Minneapolis Veterans Affairs Health Care System (MVAHCS) and the University of Minnesota-Twin Cities (UMN) [23]. The overarching goal of this prospective, longitudinal cohort study with an embedded laboratory substudy is to develop a comprehensive, multilevel model of resilience to guide the development of prevention and intervention strategies for military trainees and potentially other young people facing significant life challenges.

Figure 1 presents the basic conceptual model guiding this study [24]. It recognizes that individuals are embedded within a complex system of risk and protective factors that span multiple levels, from individual neurobiological and behavioral factors to social and broader environmental factors. This multisystemic perspective acknowledges the dynamic and reciprocal relationships among these influences and their joint impact on resilience [25]. The model also emphasizes potential pathways to risk and resilience in the face of adversity (shown as blue and red lines in response to BCT). Challenging life experiences in the past and at present, including childhood adversity or trauma and exposure to military training, can heighten the risk of developing psychopathology. As illustrated by the dotted line in Figure 1, promotive factors, such as cognitive ability and social support, directly contribute to positive adaptation, regardless of the risk level. The dashed line in Figure 1 illustrates how protective factors can act as buffers against the detrimental effects of adversity. In the ARMOR study, the focus is on investigating self-regulation as a key protective process contributing to resilience.

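### Aim 2 tests hypothesized mediators by change in model fit, which does not test an indirect effect and cannot separate a mediator from a factor linked to only one end of the pathway

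*Protocol article*

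**What the plan says.** Aim 2 is part of the primary objective. Its first approach, in Statistical Methods, adds protective and vulnerability measures to the growth mixture models accepted in Aim 1. On the role of each measure the article says: "We will treat potential predictors as moderators or mediators, depending on their hypothesized role in the model, and we will test their contribution". The same sentence fixes the yardstick: "by change in model fit indices using the Akaike information criteria (AIC), the Bayesian information criteria (BIC), root mean squared error (RMSE". A fourth measure completes the list: "goodness-of-fit (G^2^) also known as the likelihood ratio test". It does not say which paths are fixed in the smaller model and freed in the larger one.

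Three other elements of Aim 2 bear on the point:

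- The analysts will "evaluate the change in the relationships (coefficients) that indicators have with the latent trajectories". No test, interval or decision rule is attached.
- In the second approach, the factors "will be used as predictors in random intercept multinomial logistic mixed models", with trajectory class as the outcome.
- A Bayesian network analysis is to explore how the domains depend on one another.

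In the Background section, the conceptual model separates two kinds of helpful factor. One kind buffers adversity. The other acts directly: "promotive factors, such as cognitive ability and social support, directly contribute to positive adaptation, regardless of the risk level".

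**The concern.** Calling a factor a mediator means that adversity acts on the trajectory through it. Let a be the path from adversity to the factor and b the path from the factor to the outcome, given adversity. The hypothesis is a×b ≠ 0, and its null is a×b = 0. A comparison of fit has a different null, namely that every freed path is zero. The two nulls part company in two situations:

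- a ≠ 0 and b = 0. The factor correlates with adversity but does not affect the outcome. Freeing both paths improves fit, and there is no mediation.
- a = 0 and b ≠ 0. The factor affects the outcome but is not moved by adversity. Freeing the outcome path improves fit, and there is no mediation. This is the article's promotive factor.

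The mismatch remains when the models are properly nested on the same variables. It matters because Aim 2 is meant to distinguish promotive factors from protective processes, and the article's conclusions look to the findings as a basis for interventions. A directly acting factor labelled as a mechanism could misdirect that work. The criticism is confined to mediators. For a moderator, a likelihood ratio test of the interaction term is a proper test.

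**Working it through.** **The plan's own figures.** Sample Size and Power Analysis works "assuming a null RMSEA of 0.05 and an α of .05". With noncentrality λ = (n − 1) × df × RMSEA², n = 780 and df = 5, the null gives 779 × 5 × 0.0025 = 9.74. The alternative RMSEA is not stated. A value of 0.10 gives 779 × 5 × 0.01 = 38.95 and power 0.909, as stated, and it reproduces all of Table 4 to within 0.001. Also 780 / 0.65 = 1200. The power statement is not at fault, and n = 780 is carried forward.

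**Model for the check.** One standardized factor M between adversity X and a continuous outcome Y, direct effect of X on Y 0.2, 2,000 simulated samples per row. The path sizes and the direct effect are assumptions, because the article gives none. The growth mixture model itself was not simulated.

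**Criteria.** Write RSS for the residual sum of squares.

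- G²(a) = n ln(RSS of M without X / RSS of M with X).
- G²(b) = n ln(RSS of Y on X / RSS of Y on X and M).
- Both paths freed: G² = G²(a) + G²(b). It passes above 5.99 (2 df, 5%). AIC passes above 2 × 2 = 4, and BIC above 2 ln 780 = 13.32.
- Outcome path only: G²(b) passes above 3.84, AIC above 2, BIC above ln 780 = 6.66.
- Joint significance: |z| > 1.96 for both a and b.

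**Size by hand.** With b = 0, the noncentrality of the 2-df test is −780 ln(1 − a²). This is 7.84 at a = 0.10, 17.75 at 0.15 and 31.84 at 0.20. The last two lie well above 5.99.

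**Both paths freed, true indirect effect zero, n = 780 (percentage passing):**

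| a | b | G² | AIC | BIC | Joint significance |
|---|---|---|---|---|---|
| 0 | 0 | 4.2 | 14.0 | 0.0 | 0.4 |
| 0.10 | 0 | 70.1 | 83.3 | 24.9 | 3.8 |
| 0.15 | 0 | 98.0 | 99.2 | 75.4 | 4.2 |
| 0.20 | 0 | 100 | 100 | 98.2 | 5.2 |
| 0 | 0.10 | 72.1 | 85.2 | 25.7 | 4.4 |
| 0 | 0.15 | 97.6 | 99.2 | 77.7 | 5.4 |
| 0 | 0.20 | 100 | 100 | 98.8 | 5.9 |

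**Only the outcome path freed, n = 780:**

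| a | b | G² | AIC | BIC |
|---|---|---|---|---|
| 0 to 0.30 | 0 | 4.2–5.3 | 15.6–16.7 | 0.8–1.1 |
| 0 | 0.10 | 80.0 | 92.9 | 60.2 |
| 0 | 0.15 | 98.8 | 99.7 | 95.6 |
| 0 | 0.20 | 100 | 100 | 99.9 |

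**When mediation is real.** Joint significance detects it in 64% at a = b = 0.10 and in 100% at a = b = 0.20.

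**Closer to the planned outcome.** A three-class multinomial outcome was simulated with assumed class shares of 75/15/10% and an adversity log odds ratio of 0.4 per SD. With a = 0.3, b = 0 and all paths freed (3 df), G², AIC and BIC passed the non-mediator in 100% of samples. With a = 0, a log odds ratio of 0.4 for the factor and only the outcome paths freed (2 df), they passed it in 99.2%, 99.9% and 88.6%. Joint significance passed these non-mediators in 4–6%.

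**Limit of the remedy.** With an assumed common cause of factor and outcome (loading 0.4 on each), a = 0.3 and b = 0, joint significance was positive in 99.8%.

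**The case against.** A reader might infer that a factor on no causal pathway at all would be confirmed as a mediator almost every time. The documents do not support that. With neither path, G² passes about 4% and BIC about none. If only the outcome path is freed and b = 0, G² stays near 5% whatever a is. The high rates need one real path of some size and a comparison that frees it, and the article states neither.

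A reader might also infer that the article counts better fit as proof of mediation. It says only that a factor's contribution to the model will be tested, which a fit comparison does. The written Aim 2 hypotheses are about predicting class membership, and the second approach addresses those. The conceptual model stresses direct effects and buffering, and buffering is moderation.

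It can also be said that nested models and indirect-effect estimators belong in a fuller analysis plan. That would answer silence. Here the article assigns a mediator role and names the criterion for it in the same sentence, and the criterion does not fit that role.

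Nothing else in Aim 2 supplies the missing test. The multinomial models test association. The Bayesian network explores dependency structure and is given no rule for an indirect effect. The change in coefficients is descriptive. On the logit scale the adversity coefficient also shifts somewhat when a = 0, but in the multinomial simulation the median shift was only 1.5% to 4.7%, so the weightier point is that no inference is attached.

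Finally, an indirect-effect test does not protect against confounding, as the last calculation shows. That limits the remedy without making fit change a test of mediation.

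**Conclusion.** The point holds in conditional form. The stated criterion suits moderators and the choice of model structure. It does not suit mediators, because its null is not the absence of an indirect effect. This follows by logic and needs no simulation.

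The size depends on assumed paths. At n = 780, a non-mediator with one real standardized path that the comparison frees passes a 2-df G² test in about 70% of samples at 0.10, 98% at 0.15 and 100% at 0.20 or more. For BIC the figures are about 25%, 75–78% and 98–99%. Joint significance passes 4–6%. A factor with neither path, or with b = 0 when only the outcome path is freed, passes G² at about the nominal 5%. The actual rate in this study cannot be fixed from the article, because neither the path sizes nor the nested comparison is given.

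**What to change.** In the Aim 2 text of Statistical Methods:

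1. For each factor entered as a mediator, estimate the indirect effect. Claim mediation only if its bootstrap interval excludes zero, or if both the adversity-to-factor and the factor-to-outcome paths are significant.
2. State which paths are fixed and which are freed in each nested comparison.
3. Keep AIC, BIC and G² for choosing model structure and for the interaction terms of moderators.
4. State that the indirect-effect test still assumes no unmeasured confounding between mediator and outcome.

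The cost is wording and some computing time for the bootstrap. No new data are needed. Fewer factors will be labelled as mediators, and weak real mediators may be missed: at a = b = 0.10 the joint rule finds 64%.
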